### Economic evaluation

In addition to evaluating the effectiveness of point-of-care positioning of Xpert MTB/RIF, data from the trial will be combined with those from a costing analysis to explore the cost-effectiveness of point-of-care placement. Health system costs will be obtained through monitoring of study expenditure and interviews with health service management. Collection of data relating to patient and household costs will be nested within the trial—this will involve additional data collected from a subset of patients at baseline and at the 2-month follow-up to determine direct and indirect costs incurred during the diagnostic process. The framework for costing analysis is presented in Table 2. The health system costs and patient costs will be combined with the outcome data to generate an average incremental cost per TB case appropriately treated.

**Table 2 T2:** Components of cost analysis

**Health service costs**	**Patient and household costs**
**Direct costs associated with diagnostic services**	**Direct costs**
***Fixed***	***Transport***
Building space	Transport to/from clinic (patient ± carer)
Utilities	Transport to/from hospital (patient ± carer)
GeneXpert machine	***Non-transport***
Staff training	Medication
Internal/external QC	OPD attendance
GeneXpert calibration	X-rays
***Variable***	GP consultation
Xpert MTB/RIF tests	Traditional healer consultation
Consumables (gloves, N95 masks)	
Specimen transport	
Staff work time (based on time analysis)	
GeneXpert maintenance	
**Direct costs associated with medical services**	**Indirect costs**
First-line TB therapy	Lost time (salary) at work (patient ± carer)
MDR-TB therapy	
Hospital admission	
OPD attendance	
Clinic attendance	

### Operational feasibility

The study will also compare the operational feasibility of Xpert MTB/RIF implementation at the hospital laboratory and at the primary health care clinic. This encompasses an assessment of the performance and robustness of the system, as well as evaluation of the practicality of operating the system at the laboratory and at the clinic. The key indicators to be assessed are displayed in Table 3. Data on these indicators will be collected throughout the trial.

**Table 3 T3:** Indicators for operational feasibility evaluation

**Indicator**	**Method of measurement**
Power supply	Time log for power cuts/generator use
Operating temperature for GeneXpert machine	Temperature log
Storage temperature for Xpert MTB/RIF kits	Temperature log
Hands-on user time	Activity log
Indeterminate results	GeneXpert software
Data errors (incomplete identifiers etc.)	GeneXpert software
Maintenance needs	Requirement for supplier support
Training requirements	Recording of initial and follow-up training sessions
Supervision requirements	Log of assistance from other laboratory staff/PI
Waste management	Recording of problems with disposal of used cartridges
User appraisal	Regular appraisal by laboratory staff and study staff
User performance	Regular independent observation of staff performance

### Ethical considerations

The study has been approved by the Biomedical Research Ethics Committee of the University of KwaZulu-Natal (BF033/11), the Ethics Committee of the London School of Hygiene and Tropical Medicine (5926), and the Health Research Committee of the KwaZulu-Natal Department of Health (HRKM084/11). Permission for the study was granted by Hlabisa Hospital and by the Community Advisory Board of the Africa Centre for Health and Population Studies.

Given that the units of randomisation are time blocks, it is not possible for individuals to consent to randomisation. Individual consent for participation remains important given that the intervention is delivered to individuals and that individual-level data are collected at enrolment and at follow-up.

There are TB suspects who are not eligible for this study and therefore will not have access to Xpert MTB/RIF testing within the study (suspects who are neither HIV-infected nor at high risk for MDR-TB). The justification for this is that these groups were a lower priority for this intervention given the much lower mortality rates and these suspects continue to receive diagnostic evaluation including sputum microscopy ± culture/LPA/DST according to national guidelines. At the time of study design it was predicted that, were Xpert MTB/RIF to be implemented in South Africa, the WHO recommendations would be followed (use in HIV-infected and those at high risk of MDR-TB). Although the national roll-out plan went beyond this in incorporating its use for all TB suspects, Xpert MTB/RIF has not yet been installed in Hlabisa sub-district and is therefore not yet available in the sub-district outside the trial.

## Discussion

Evaluation of diagnostic tools provides different challenges than those of therapeutic interventions. Diagnostic accuracy studies are usually the starting point for evaluation of new technologies, yet to inform public health policies and implementation it is crucial to evaluate patient-important outcomes [30]. The ultimate impact of a new diagnostic test should be measured by its capacity to generate beneficial outcomes. A randomised trial is the most rigorous design to evaluate clinical outcomes from a diagnostic intervention. Individual randomisation was considered logistically challenging and potentially disruptive in the context of a busy clinic and laboratory system, although this would have been the most efficient statistical design [28]. Cluster randomisation by health care facility was not possible given the limited resources. Therefore cluster randomisation by time block was the preferred study design to maximise internal validity and to minimise disruption to clinic services. Other trial designs were considered (non-randomised controlled trial with allocation by day/week/month or controlled before and after study) but were felt to be inferior in addressing the research hypothesis, mainly because of the potential for bias and therefore loss of internal validity. There have been few published trials where the unit of randomisation is a time block rather than a geographical or organisational cluster. The trials that have been published have not used consistent methods for sample size calculation—some have adjusted appropriately for cluster variation [31-33] whereas others have arbitrarily inflated the sample size from that for an individual RCT [34] and others have based the sample size on the numbers available to participate [35].

Blinding of patients or of health care workers is not feasible in this pragmatic diagnostic trial because allocation to trial arms involves different actions by the patient and the clinical staff. As a result of this, the outcomes are as objective as possible to limit potential bias from differential ascertainment of outcomes in the two arms. The possibility of differential recruitment into the trial arms exists but will be minimised by standardised referral criteria for the clinic health care workers; recruitment will be monitored by reviewing the clinic records to ascertain what proportion of patients with cough were referred to the study during each 2-week block. This will be reported if there is a major imbalance in recruitment to the two trial arms. There is a further risk of selection bias if there is differential non-participation. The proportions of eligible subjects consenting by trial arm will be monitored and will be reported accurately at the conclusion of the trial. There is some risk of contamination between the arms if, over time with point-of-care testing, the health workers see the importance and the effect of receiving the test result in a timely fashion and this then improves their ability to encourage all suspects to return and receive their result. This would tend to bias the findings towards the null hypothesis. We will explore this by assessment of the variability in the proportion returning for their test result by cluster and by time period.

The evaluation of diagnostic accuracy is not the primary focus of the trial and the reference standard of a single culture could be considered an imperfect gold standard. In the initial Xpert MTB/RIF clinical validity studies, the reference standard used results of liquid and solid culture on two specimens (four culture results in total) [17]. Conversely, in the later demonstration studies, the reference standard varied between study sites and in some sites included results of only a single culture [18]. Observational data from the district in 2007 suggested that 5% of all culture-positive cases were multidrug-resistant [36]. Given that we will preferentially include suspects with a high risk of MDR-TB, we expect the overall proportion with MDR-TB to be at least 10%. It is possible that the impact of Xpert MTB/RIF positioning may be different for the drug-susceptible and drug-resistant cases. If this is the case then a higher or lower than expected proportion with MDR-TB could modify the effect of point-of-care placement, and this will be explored in secondary analyses.

There are a number of trials evaluating the impact of Xpert MTB/RIF in different settings and with different research hypotheses. Information about research projects is collated by the TREAT TB Xpert Research Mapping Project [37]. Several studies are examining point-of-care implementation but, to our knowledge, this is the only study directly comparing point-of-care use to centralised laboratory use. There is already some evidence from South Africa of the feasibility of implementation at the primary health care level, although several operational challenges were experienced when implemented within a very large urban clinic [38,39]. This study should provide direct evidence of any benefits of point-of-care positioning as well as further information about the costs and logistical challenges of such strategies. This can also be considered as a proof-of-principle study that will help to understand the benefits of bringing diagnostics closer to patients, and this will have broader relevance as we continue to develop and evaluate diagnostic technologies suitable for point-of-care use [40,41].

## Trial status

The study received final ethical approval in June 2011. Enrolment commenced on 22 August 2011. Enrolment is scheduled to complete in March 2013 and follow-up will be complete in May 2013.

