### Study design

The study is a pragmatic cluster randomised clinical trial comparing two positioning strategies for the Xpert MTB/RIF system: positioning at centralised laboratory level (district hospital laboratory) versus positioning at primary health care clinic level (point of care). The cluster (unit of randomisation) is a 2-week time block at the primary health care clinic (clinic blocks), and clusters are randomly assigned to the district hospital laboratory strategy or point-of-care strategy. The trial schema is shown in Figure 2.

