### Sample size

The study was designed to detect an increase from 85% to 95% in the proportion of culture-confirmed pulmonary TB cases initiated on appropriate treatment within 30 days. Sample size was calculated with the equation of Hayes and Bennett, using the coefficient of variation (κ) [26]. With κ = 0.05 and a cluster size of 12 culture-positive cases, we would need 16 clusters and 188 culture-positive TB cases in each arm to detect this difference with 95% confidence and 80% power. We assumed 10% of individual participants would be lost to follow-up at 60 days, so we would need 208 culture-positive TB cases in each arm. Based on the assumption that 25% of TB suspects would have a positive MGIT culture, we would require enrolment of 1,664 TB suspects. The total sample size will therefore be 32 clusters and 1,664 individual participants.

The coefficient of variation (κ) is small, but as the clusters are clinic time blocks rather than geographic areas or health care facilities, minimal variation is expected between clusters. This value of κ corresponds to a range of proportions appropriately treated within 30 days in the district hospital laboratory arm of 77-94%.

For the secondary endpoint of all-cause mortality within 60 days, the analysis will incorporate all participants (all suspects), regardless of presence or absence of TB disease. The sample size of 32 clusters and 60 participants per cluster gives approximately 80% power to detect a 33% reduction in mortality from 12% in the district hospital laboratory arm to 8% in the point-of-care arm, with 95% confidence.

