### Outcome evaluation

To ascertain the primary and secondary outcomes, at enrolment all participants are allocated a review date 2 months from the enrolment visit. Participants are invited to attend clinic for review but are also invited to consent to telephonic follow-up and/or home visit in case clinic visit is not possible. Additional contact details are provided for at least one other family member (or other person designated by participant) at enrolment, wherever possible. Participants are told that, when attending the clinic for the follow-up visit, they will be reimbursed with a ZAR 50 grocery voucher (approximately equivalent to USD 6). Outcome data pertaining to TB treatment initiation, additional investigations, hospital attendances and admissions, and ART initiation (where appropriate) are collected on a case report form by the study nurse. In the event that no contact is made with patient or with named contact persons, follow-up information is collected from the clinic TB registers and the operational HIV programme database – permission to use these data is also included in the informed consent process.

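### The 80% mortality power assumes 1,920 participants, but the plan enrols 1,664 (about 73–76% power); the 32 two-week clusters are also not reconciled with enrolment to March 2013

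*Protocol article*

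**What the plan says.** All places are in the protocol article.

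- **Study design:** "The cluster (unit of randomisation) is a 2-week time block at the primary health care clinic". Under Setting, participants come from a single clinic.
- **Sample size, primary outcome:** 85% v 95%, coefficient of variation 0.05, 12 culture-positive cases per cluster, 16 clusters and 188 cases per arm. This becomes 208 per arm for 10% loss to follow-up. With 25% of suspects culture-positive, the text concludes: "The total sample size will therefore be 32 clusters and 1,664 individual participants".
- **Sample size, 60-day mortality in all suspects:** "The sample size of 32 clusters and 60 participants per cluster gives approximately 80% power" for 12% v 8%. No coefficient of variation is given for this outcome.
- **Randomisation:** permuted blocks of eight. Each envelope is opened on the Friday before a new block and gives the allocation for the following two weeks.
- **Trial status:** "Enrolment commenced on 22 August 2011" and "Enrolment is scheduled to complete in March 2013", with the end of follow-up given as May 2013.
- **Outcome evaluation:** "at enrolment all participants are allocated a review date 2 months from the enrolment visit".

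**The concern.** Two sets of figures do not fit together.

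First, the mortality calculation uses a cluster size that the planned total cannot supply: 1,664 / 32 = 52, not 60. Mortality is the first-listed secondary outcome and the only one with its own power statement. A reader who later sees a non-significant mortality result would judge it against a power that the planned enrolment does not give.

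Second, with one clinic and clusters defined as two-week periods, the calendar largely determines how many clusters there are. The enrolment period holds more two-week periods than the 32 stated. The number of clusters is the number of randomised units, so a reader needs to know which figure describes the trial.

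**Working it through.** **Formula.** The plan cites Hayes and Bennett. For proportions, the clusters per arm are

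c = 1 + (z₀.₉₇₅ + z₀.₈₀)² · V / (p0 − p1)², with V = [p0(1−p0) + p1(1−p1)]/m + κ²(p0² + p1²).

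Inverted for power: Φ( √[(c − 1)(p0 − p1)²/V] − 1.960 ).

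**1. Reproduce the primary figure.** With p0 = 0.85, p1 = 0.95, m = 12 and κ = 0.05:
- V = (0.1275 + 0.0475)/12 + 0.0025 × (0.7225 + 0.9025) = 0.01865.
- c = 1 + 7.849 × 0.01865/0.01 = 15.63, so 16 clusters per arm; 15.63 × 12 = 187.6, so 188 cases. Both match the plan.
- 188/0.9 = 208.9 (stated as 208); 416/0.25 = 1,664; 1,664/32 = 52 suspects, or 13 culture-positive cases, per cluster (11.7 after 10% loss).
- Power with 16 per arm is 81.0% at m = 12 and 80.2% at m = 11.7.

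**2. Reproduce the mortality figure.** With p0 = 0.12, p1 = 0.08, c = 16 and m = 60, and κ = 0.05 borrowed from the primary outcome:
- V = (0.1056 + 0.0736)/60 + 0.0025 × (0.0144 + 0.0064) = 0.003039.
- √(15 × 0.0016/0.003039) = 2.810; Φ(2.810 − 1.960) = 80.2%.
- It is 80.9% at κ = 0 and 78.3% at κ = 0.10. The stated figure therefore reproduces at small κ, but only with 32 × 60 = 1,920 participants, 256 more than planned.

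**3. Mortality power at the planned 1,664.** At m = 52 and κ = 0.05, V = 0.003498 and Φ(2.619 − 1.960) = 74.5%. Over the range of κ and cluster numbers:

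| Clusters | Per cluster | κ = 0 | κ = 0.05 | κ = 0.10 |
|---|---|---|---|---|
| 32 | 52 | 75.1% | 74.5% | 72.7% |
| 40 | 41.6 | 75.7% | 75.2% | 73.7% |
| 42 | 39.6 | 75.8% | 75.3% | 73.9% |
| 32, after 10% loss | 46.8 | 70.7% | 70.1% | 68.4% |
| 40, after 10% loss | 37.4 | 71.2% | 70.8% | 69.4% |

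The number of clusters hardly matters here. The shortfall comes from the number of participants.

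**4. Calendar.** 22 August 2011 is a Monday. Assuming consecutive 14-day blocks:
- 32 blocks (64 weeks) end on Friday 9 November 2012.
- 40 blocks end on Friday 1 March 2013, and 42 on Friday 29 March 2013.
- The gap is 16–20 weeks, or 8–10 blocks.
- May 2013 is March plus the two-month review, so March 2013 does not look like a misprint.

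**5. Primary power under the longer schedule.** With 1,664 participants, 25% culture-positive and 10% lost:
- 40 blocks: 1,664/40 × 0.25 × 0.9 = 9.36 cases per block, and power is 82.4%.
- 42 blocks: 8.91 cases per block, and power is 82.8%.

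**The case against.** **The calendar point rests on an unstated premise.** No section says that blocks run without a break. The Randomisation section suggests it, since each Friday opening covers the next two weeks, but unenrolled weeks would leave 32 clusters intact. The Sample size section is also a design calculation, whereas Trial status is a forecast written after enrolment began, and a condensed article may leave pauses or extensions to the full protocol. This stands. It limits the calendar point to an unexplained difference, not a proven error.

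**Mortality is secondary and its power is given only as approximate.** This is true, and the trial is not sized on it. But 73–76% is not about 80%, and the cause is visible within one section, where 60 per cluster and 1,664 in 32 clusters cannot both hold.

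**The 10% loss may overstate missing deaths.** The Outcome evaluation section provides for contact persons, registers and the HIV programme database. That is fair. The figures without loss are therefore the main result, and those after loss are a lower case.

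**The stronger reading.** A reader might infer that the longer schedule means slower accrual, so that stopping after 32 blocks would leave the primary analysis short of 80%. The documents do not support this. It takes an accrual rate from reaching 1,664 by March 2013 and then stops in November 2012 short of 1,664. No section describes such a stop.

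**Conclusion.** The mortality power statement is wrong as written. At the planned 1,664 participants it is about 73–75% in 32 clusters and 74–76% in 40–42, against a stated figure of about 80%. After 10% loss it is about 68–71% in 32 or 40 clusters. These results rest on the Hayes-Bennett formula and on an assumed κ of 0–0.10, because the article gives none for mortality. A larger κ would lower them further. This conflict lies within the Sample size section and does not depend on the enrolment dates.

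The mismatch between 32 clusters and the 40–42 block-lengths up to March 2013 is real if blocks are contiguous, and it is unexplained. It needs reconciling, but it does not show that either figure is wrong.

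The primary sample size and power stand. The plan's figures reproduce, and the stated 80% is met both at 32 clusters and with 1,664 participants spread over 40–42.

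**What to change.** 1. In the Sample size section, restate the mortality power and the cluster size for the 1,664 participants planned, and give the coefficient of variation used for mortality. With 32 clusters this means 52 per cluster and about 73–75% power before loss, for κ of 0–0.10. Say whether loss to follow-up is included.
2. Reconcile the block count with the enrolment dates in one sentence. State either the number of blocks to be run (40 would be five complete permuted blocks of eight, ending on 1 March 2013) or that blocks were paused and 32 stands. If the count changes, restate the cluster size to match.

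The cost is wording and a short recalculation. No extra patients are needed and the primary analysis is unchanged. The stated mortality power becomes less favourable.

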## Abbreviations

ART: Antiretroviral therapy; DST: Drug susceptibility testing; GEE: Generalised estimating equation; HIV: Human immunodeficiency virus; MDR-TB: Multidrug-resistant TB; MGIT: Mycobacterial growth indicator tube; NHLS: National Health Laboratory Service; PCR: Polymerase chain reaction; PHC: Primary health care; TB: Tuberculosis; WHO: World Health Organization; XDR-TB: Extensively drug-resistant TB.
